#### Missing data

No imputation of missing data is planned. Loss to follow-up will be characterised by comparing baseline sociodemographic and clinical variables between participants who complete the study and those lost to follow-up. Sensitivity analyses will be conducted to assess the potential impact of missing data on the main outcomes.

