**Trial registration number:**

NCT07068945.

STRENGTHS AND LIMITATIONS OF THIS STUDYDual-source design combining administrative data (French National Institute of Statistics and Economy Studies/*Programme de médicalisation des systèmes d’information* (PMSI)) with prospective longitudinal follow-up.Standardised validated instruments (Mini International Neuropsychiatric Interview—simplified (MINI-S), WHO Quality of Life—brief (WHOQOL-BREF), Health of the Nation Outcome Scales for Children and Adolescents (HoNOSCA), Transition Readiness and Appropriateness Measure (TRAM) and Transition Related Outcome Measure (TROM)) are administered repeatedly over 12 months.Consecutive recruitment includes adolescents receiving outpatient, inpatient and emergency psychiatric care.The monocentric cohort design and sample size (n=100) may limit external generalisability.Attrition over 12 months may introduce bias if loss to follow-up is associated with clinical severity or care disengagement.

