#### Secondary outcomes

Annual prevalence of 17-year-old patients living in the municipality of Nice who attend the child and adolescent psychiatry services (Lenval University Children’s Hospital) in 1 year, expressed as the proportion of these patients relative to the total number of minors (<18 years) consulting in the hospital during the same year (psychiatric clinical population).Baseline description of patient profiles in the prospective cohort (n=100), including sociodemographic and medical characteristics.Care trajectories at 12 months, categorised as:Continued care in child and adolescent psychiatry.Transfer to adult psychiatry.Discontinuity or interruption/resumption of care during follow-up.Care formally discontinued in agreement between patient and care team.Lost to follow-up.Clinical evolution assessed using the MINI questionnaire at baseline (M0), 6 months (M6) and 12 months (M12), focusing on status. Additional outcomes include quality of life (WHOQOL-BREF) and care needs/psychosocial difficulties (HoNOSCA) scores at the same time points.Readiness and outcome of transition: measured with the TRAM at M0 and M6, and the TROM at M12.Continuity of psychiatric care at 12 months, defined as ‘effective’ if the patient has a structured care plan in place or has recovered and no longer requires follow-up. This binary outcome (yes/no) will be determined by the investigator based on patient evaluation. Predictors of continuity will include prespecified baseline variables selected on clinical relevance and prior literature, including sex, living situation, psychiatric history, current diagnostic profile (MINI-S), quality of life (WHOQOL-BREF), care needs and psychosocial difficulties (HoNOSCA) and transition readiness (TRAM).

Active recontact procedures (phone/SMS/email reminders and, when relevant, parental contact) will be used to limit attrition. Participants will be considered lost to follow-up only if no contact can be re-established and no information on ongoing care can be obtained.

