### Sample size estimation

Reliable local prevalence data on 17-year-olds at the transition boundary between child and adult mental health services are currently lacking. The present study addresses this gap through an epidemiological component based on INSEE census counts and PMSI hospital discharge data.

For the prospective cohort, the target sample size (n=100) was determined a priori using a feasibility-based approach. It was informed by the annual number of 17-year-olds receiving psychiatric care at Lenval University Children’s Hospital (approximately 160–200 per year), expected consent and participation rates observed in previous local non-interventionnal studies involving human participants (Recherche Impliquant la Personne Humaine, category 3 under the French regulatory framework), and the practical feasibility of recruitment within an 18-month inclusion period. This sample size is expected to provide adequate precision for descriptive estimates of clinical and sociodemographic characteristics and to support exploratory multivariable analyses examining factors associated with continuity of care at 12 months. Given the exploratory nature of secondary analyses, effect-size assumptions for formal power calculations were not available; therefore, sample size was primarily driven by feasibility and the objectives of estimation and model exploration.

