#### Secondary outcomes

Prevalence relative to the broader clinical population of minors (<18 years) attending Lenval psychiatry services.Patient profiles at baseline: descriptive statistics for sociodemographic and clinical variables.Care trajectories over 12 months: described using absolute and relative frequencies.Clinical assessments (MINI-S, WHOQOL-BREF, HoNOSCA): summarised at baseline, 6 months and 12 months; visualised using histograms and line graphs.Transition readiness (TRAM) and outcomes (TROM): summarised with means, SD, medians and IQRs; visualised by domains.

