## Discussion

This study has several strengths. Its prospective longitudinal design focuses on a critical developmental stage, while the use of validated assessment tools (MINI-S, WHOQOL-BREF, HoNOSCA, TRAM, TROM) ensures methodological rigour and comparability with international work. By combining administrative data (INSEE, PMSI) with individual clinical follow-up, the study will provide a comprehensive picture of transition needs across all public child psychiatry services in a large French city.

Importantly, the study will address a gap in French epidemiology by providing the first city-level estimate of the annual prevalence of 17-year-olds accessing specialised CAMHS. This is essential for quantifying service needs at the transition boundary and informing resource planning. Although based on PMSI 2024 data, it offers a robust 1-year snapshot based on routinely collected administrative records; year-to-year variability cannot be assessed within the present dataset.

Some limitations must be acknowledged. The single-centre design and modest sample size (n=100) may restrict generalisability and limit the power of multivariable analyses. Anticipated loss to follow-up at 12 months also reflects the challenges inherent in transitional psychiatry.^21^ In addition, the absence of a control group or multicentre setting constrains external comparisons.

Although young people and parents were not directly involved in the design of this protocol, their needs and concerns routinely observed in clinical practice strongly informed the choice of outcomes and follow-up procedures. Adolescents and families frequently express anxiety regarding the transition to adult services, including fears of losing established therapeutic relationships, uncertainty about the functioning of adult-oriented services and concerns about changes in parental involvement after the age of 18. Clinicians also observe that periods of educational, social or familial instability may increase the risk of disengagement from care, particularly among young people with evolving or non-stabilised psychiatric presentations. These observations are broadly consistent with the international literature^5
6

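### Patients lost to follow-up have no assigned value in the yes/no continuity outcome, and visit-by-visit score summaries compare different patients, so both analyses default to available cases where loss may be informative

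*Protocol article*

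**What the plan says.** All references are to the protocol article.

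- **Missing data:** "No imputation of missing data is planned". The section adds "Loss to follow-up will be characterised by comparing baseline sociodemographic and clinical variables between participants who complete the study and those lost to follow-up" and "Sensitivity analyses will be conducted to assess the potential impact of missing data on the main outcomes". It names no method and does not say which outcomes are the main ones.
- **Outcomes, Secondary outcomes:** there are five care trajectories at 12 months. Loss to follow-up is one of them, separate from discontinuity or interruption. After active recontact attempts, "Participants will be considered lost to follow-up only if no contact can be re-established and no information on ongoing care can be obtained". Continuity at 12 months is a separate yes/no outcome, rated by the investigator from an evaluation of the patient. A structured care plan, or recovery without further need of care, counts as yes.
- **Continuity of care analyses:** this binary outcome, worded here as a defined plan against no defined plan, goes into logistic regression. Patients lost to follow-up are not mentioned.
- **Statistical analysis, Secondary outcomes:** the three clinical instruments are "summarised at baseline, 6 months and 12 months; visualised using histograms and line graphs".
- **Strengths and limitations:** "Attrition over 12 months may introduce bias if loss to follow-up is associated with clinical severity or care disengagement". The Discussion adds "Anticipated loss to follow-up at 12 months also reflects the challenges inherent in transitional psychiatry".

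**The concern.** A patient with no contact and no information cannot be evaluated. With no imputation and no coding rule, the natural reading is that such a patient has no continuity value and is left out of the regression. The other wording of the outcome, defined plan against no defined plan, would allow the same patient to be coded no. The text supports both codings, and they can give materially different results.

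The clinical-course objective has a related weakness. Visit summaries joined by line graphs invite the reader to see change over time, but the baseline mean includes everyone and the 12-month mean includes only those assessed. This gap is wider than formal loss to follow-up: a patient whose care status is traced but who misses the visit also has no scores.

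At stake are the continuity proportion, the factors reported as associated with continuity, and the description of clinical course. The Discussion intends to use such results to identify young people at risk of disengagement.

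**Working it through.** **Inputs from the article.** The cohort size is 100: "the target sample size (n=100) was determined a priori using a feasibility-based approach". No power, precision or dropout formula lies behind it, so there is no stated figure to reproduce. The article gives no study-specific loss rate and no expected continuity rate.

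**Assumptions.** Loss of 10% to 40%, continuity of 40% to 60% among those followed, and the loss patterns and score gaps below.

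**1. Continuity proportion.** Let L be the number lost out of 100 and p the continuity among those seen.

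- Available cases: p, whatever L is.
- All lost counted as no: p × (100 − L) / 100.
- All lost counted as yes: [p × (100 − L) + L] / 100.
- Distance between the two bounds: L / 100, which is the loss rate.

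| Lost of 100 | Seen with continuity | Available cases | Lost = no | Lost = yes |
|---|---|---|---|---|
| 10 | 54/90 | 60% | 54% | 64% |
| 20 | 48/80 | 60% | 48% | 68% |
| 25 | 45/75 | 60% | 45% | 70% |
| 30 | 42/70 | 60% | 42% | 72% |
| 40 | 36/60 | 60% | 36% | 76% |

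For 45/75 the Wilson 95% CI is 48.7% to 70.3%. The lower bound of 45% lies outside it, so the interval does not convey this uncertainty. With p = 50%, the bounds run from 45% to 55% at 10 lost and from 30% to 70% at 40 lost. With p = 40%, they run from 36% to 46% and from 24% to 64%.

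**2. Odds ratios.** Take two predictor groups of equal size with true continuity of 60% and 40%. The true OR is (0.60/0.40) / (0.40/0.60) = 2.25. Assume 10% of patients with continuity are lost in each group, and vary the loss among those without.

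- 40% lost in both groups: (0.54/0.24) / (0.36/0.36) = 2.25. The OR is unchanged, although the available-case proportion is 60% against a true 50%.
- 20% lost in the first group and 50% in the second: (0.54/0.32) / (0.36/0.30) = 1.41.
- 50% lost in the first group and 20% in the second: (0.54/0.20) / (0.36/0.48) = 3.60.

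Total loss is 25%, 24% and 21% respectively. Loss that depends on outcome alone leaves the OR intact. Loss that depends jointly on outcome and predictor moves it either way. Counting the lost as no gives (0.54/0.46) / (0.36/0.64) = 2.09 in all three cases. That is not exact, but it is steadier here.

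**3. Score means.** If a fraction d is missing at 12 months and those patients had baseline scores g points higher than the rest, the mean falls by d × g with no patient changing. With g = 4 HoNOSCA points, this is 0.15 × 4 = 0.6, 0.25 × 4 = 1.0 and 0.30 × 4 = 1.2. With g = 2 and d = 0.25 it is 0.5. The article gives no basis for g, so these values show only the mechanism.

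**The case against.** The strongest reply is that the article already covers much of this.

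- **Disengagement is recorded.** A reader might infer that it disappears from the data. It does not: discontinuity and loss to follow-up are both reported as trajectories, and the definition of loss is narrow. A disengaged patient who can be traced is not lost and can be rated no. This stands, and it limits the problem to the untraceable remainder and to missed score visits.
- **Exclusion is not stated.** No section says that lost patients leave the regression. This also stands: exclusion is the default reading, not a written rule.
- **Lost means unknown.** Some lost patients may have recovered or be in care elsewhere, and both could count as continuity. So an upward bias in the proportion is likely but not certain. The analysis section promises odds ratios and does not itself list a continuity rate, although continuity at 12 months is a named outcome.
- **Sensitivity analyses are promised.** Their detail may properly sit in an analysis plan that is not shown, so its absence is not the complaint. But the article does fix the main approach: no imputation and visit-wise summaries. An unnamed sensitivity analysis on undefined main outcomes leaves that approach unchanged. Comparing the baseline of completers and lost patients describes selection without correcting it.
- **Imputation would not be a cure.** This is correct. Standard multiple imputation assumes data missing at random and would not repair loss caused by disengagement itself. The missing mapping matters more than the absence of imputation.
- **The clinical-course analysis is descriptive.** This is true, but a descriptive line graph across changing patient sets will still be read as change.

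**Conclusion.** The point holds in a limited form. As written, the continuity regression and the 6- and 12-month score summaries default to available cases, in a study whose authors warn that loss may follow severity or disengagement. If it does, the continuity proportion is probably too high. With 25 of 100 lost and 60% continuity among those seen, both assumed, 60% would be read where the data allow 45% to 70%. The uncertainty equals the loss rate, whatever that turns out to be.

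A reader might go further and conclude that odds ratios are necessarily pulled towards 1. The documents do not support that: a true 2.25 can stay at 2.25, fall to 1.41 or rise to 3.60, depending on a loss pattern nobody can know in advance. Spurious improvement in scores is possible, but its size cannot be derived from the article.

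Only secondary, exploratory objectives are affected. The primary outcome rests on administrative counts and is untouched. The change should be made, but the study does not depend on it.

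**What to change.** 1. State how each of the five trajectories, including loss to follow-up, maps to continuity yes or no, and use one wording of the outcome in both the Outcomes and the analysis sections.
2. Report the continuity proportion on all 100 participants, with lost = no and lost = yes as bounds.
3. Name the regression with lost = no as a prespecified sensitivity analysis. Multiple imputation using baseline and 6-month data may be added, with the statement that it is valid only under missing at random.
4. Base conclusions on clinical course on change estimated from all observed visits: a repeated-measures mixed model for WHOQOL-BREF domains and HoNOSCA total, and a binary mixed model for MINI-S status, each with 95% CIs. These also assume missing at random given the observed data. Keep the visit summaries as description, with the number assessed shown at each visit.

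The cost is protocol wording and some programming, and the continuity rate may look less favourable. No new data are needed. Recruitment began on 7 April 2026 and follow-up lasts 12 months, so no 12-month outcome is due before about April 2027, and the rules can be fixed before those results are known.

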### Data management

Study data will be collected using a dedicated case report form (CRF), developed in collaboration with the study sponsor’s clinical research associate and the data manager of the Clinical Research and Innovation Department (DRCI) of Nice University Hospital, under the supervision of the principal investigator. Data will be entered directly into an electronic CRF (e-CRF) created with Research Electronic Data Capture, which will be configured and maintained by the DRCI.

Investigators, supported by the study clinical research associate, will be responsible for accurate data entry and ongoing verification. Access rights to the e-CRF will be restricted according to user roles. Data quality will be ensured through programmed consistency checks and monitoring procedures, with any queries resolved in collaboration with investigators.

At the end of the study, the database will be locked (‘frozen’) once validation checks are complete and signed off by the principal investigator, the data manager, and the study statistician. The locked dataset will then be transferred for statistical analysis.

### Ethics and dissemination

The study received ethical approval from the Comité de Protection des Personnes Sud-Ouest et Outre-Mer IV (CPP, French research ethic committee), approval number 2025-A01581-48. In accordance with French regulations, the study is classified as a minimal-risk interventional research project. Written informed consent will be obtained from all participants and their legal guardians prior to inclusion. Participant data will be collected and processed in accordance with applicable confidentiality and data-protection regulations, including the General Data Protection Regulation. Data will be pseudonymised prior to analysis, stored on secure servers with restricted access and retained for the legally required duration. The trial is registered at ClinicalTrials.gov (NCT07068945). Study findings will be disseminated through peer-reviewed publications, presentations at national and international scientific conferences and reports to relevant health authorities.

## Discussion

This study has several strengths. Its prospective longitudinal design focuses on a critical developmental stage, while the use of validated assessment tools (MINI-S, WHOQOL-BREF, HoNOSCA, TRAM, TROM) ensures methodological rigour and comparability with international work. By combining administrative data (INSEE, PMSI) with individual clinical follow-up, the study will provide a comprehensive picture of transition needs across all public child psychiatry services in a large French city.

Importantly, the study will address a gap in French epidemiology by providing the first city-level estimate of the annual prevalence of 17-year-olds accessing specialised CAMHS. This is essential for quantifying service needs at the transition boundary and informing resource planning. Although based on PMSI 2024 data, it offers a robust 1-year snapshot based on routinely collected administrative records; year-to-year variability cannot be assessed within the present dataset.

Some limitations must be acknowledged. The single-centre design and modest sample size (n=100) may restrict generalisability and limit the power of multivariable analyses. Anticipated loss to follow-up at 12 months also reflects the challenges inherent in transitional psychiatry.^21^ In addition, the absence of a control group or multicentre setting constrains external comparisons.

Although young people and parents were not directly involved in the design of this protocol, their needs and concerns routinely observed in clinical practice strongly informed the choice of outcomes and follow-up procedures. Adolescents and families frequently express anxiety regarding the transition to adult services, including fears of losing established therapeutic relationships, uncertainty about the functioning of adult-oriented services and concerns about changes in parental involvement after the age of 18. Clinicians also observe that periods of educational, social or familial instability may increase the risk of disengagement from care, particularly among young people with evolving or non-stabilised psychiatric presentations. These observations are broadly consistent with the international literature^5
6
22^ and contributed to our decision to include measures of transition readiness, continuity of care, quality of life and care trajectories. Future iterations of the project will integrate formal patient and public involvement to further strengthen the relevance and acceptability of transition pathways.

Despite these limitations, the Odyssée project is expected to yield valuable insights. Clinically, it should help identify patients at risk of disengagement and inform structured interventions to support continuity of care. Organisationally, beyond providing descriptive epidemiological data, the study is intended to serve as a foundation for building a dedicated care pathway and specialised team to address the specific needs of young people during the transition to adult psychiatry. At a broader level, the findings will inform regional planning and may serve as a pilot model for replication in other regions, contributing to the international literature on transitional mental healthcare.^35
36^

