**Methods and analysis:**

This prospective monocentric cohort study will be conducted at Lenval University Children’s Hospital in Nice, the only paediatric hospital providing dedicated child psychiatry emergency services in the Alpes-Maritimes department. Recruitment started in April 2026 and is ongoing at the time of manuscript submission. Study completion is anticipated in September 2028. The primary objective is to determine the annual prevalence of 17-year-olds living in Nice who attend child and adolescent psychiatry services using administrative data combining census counts from the French National Institute of Statistics and Economy Studies and hospital discharge records (*Programme de médicalisation des systèmes d’information* (PMSI)).

In parallel, a prospective cohort of 100 adolescents aged 17 years will be followed for 12 months to address secondary objectives, including clinical profiles, care trajectories, transition readiness, clinical outcomes and determinants of care continuity. Assessments will be conducted at baseline, 6 months and 12 months using validated instruments (Mini International Neuropsychiatric Interview—simplified (MINI-S), WHO Quality of Life-brief (WHOQOL-BREF), Health of the Nation Outcome Scales for Children and Adolescents (HoNOSCA), Transition Readiness and Appropriateness Measure (TRAM), Transition Related Outcome Measure (TROM)). Descriptive and multivariable analyses will be performed to identify factors associated with continuity of care. This study is expected to provide one of the first city-level estimates of psychiatric transition needs in France and contribute to the international literature on continuity of care, youth mental health trajectories and transitional service organisation.

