## Objectives

The primary objective of this study is to determine the annual prevalence of 17-year-old patients living in the city of Nice who consult specialised CAMHS child and adolescent psychiatry services, relative to the total population of 17-year-olds residing in Nice.

The secondary objectives are to:

Estimate the annual prevalence of 17-year-olds living in Nice who consult specialised CAMHS (Nice University Children’s Hospital(HPU Lenval)), relative to the population of minors (<18 years) in psychiatric clinical care.Describe the clinical and sociodemographic profiles of a sample of 17-year-old patients living in Nice and consulting specialised CAMHS (HPU Lenval).Characterise care trajectories over a 12-month follow-up period, according to the evolution of clinical management.Assess the clinical course of patients during follow-up.Evaluate the level of readiness for transition to adult psychiatry.Identify factors associated with continuity of psychiatric care at 12 months.

Taken together, these objectives aim to generate actionable local evidence to tailor transition planning and service organisation to the specific needs of young people in Nice. Findings will inform locally adapted tools and dedicated pathways to improve continuity of care across the CAMHS–AMHS transition.

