#### Inclusion criteria

Participants must meet all of the following criteria:

Age ≥17 and <18 years at inclusion.Receiving care (outpatient, inpatient or emergency) within the Child and Adolescent Psychiatry Department at Lenval University Children’s Hospital.Presence of a psychiatric disorder according to Diagnostic and Statistical Manual of Mental Disorders, Fifth Edition (DSM-5) criteria, irrespective of diagnostic category.Considered to be in a potential transition situation to adult mental health services within the following 12 months.Living in the municipality of Nice (postal codes 06000, 06100, 06200, 06300).Able to provide written informed consent, together with at least one parent or legal guardian.

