### Recruitment and informed consent

Eligible adolescents and their parents or legal guardians will receive written and oral information about the study from a member of the research team who is not directly involved in the patient’s clinical care. Potential participants are identified consecutively by clinicians within the Child and Adolescent Psychiatry Department during routine outpatient consultations, inpatient admissions, day hospital care or emergency psychiatric assessments. Screening logs are maintained to document the number of eligible patients approached, included or refusing participation during the recruitment period. To ensure voluntary participation, a minimum 72-hour reflection period will be respected between information and consent. At inclusion (age 17), written informed consent will be obtained from at least one parent or legal guardian, together with the adolescent’s written assent. In accordance with French regulations governing minimal-risk interventional research involving minors, parental consent remains mandatory until participants reach the age of 18 years. When participants turn 18 during follow-up, renewed written consent will be obtained to continue participation. Participation or refusal will have no impact on clinical care, and withdrawal is possible at any time without consequences.

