### Outcomes

#### Primary outcome

The primary outcome is the annual prevalence of 17-year-old patients living in the municipality of Nice who attend the child and adolescent psychiatry services at Lenval University Children’s Hospital, defined as the number of 17-year-olds consulting in 1 year divided by the total number of 17-year-olds living in the general population of Nice.

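### The primary figure counts any psychiatric contact at one hospital, but the article presents it as CAMHS use in general and claims city-level transition need across all public services

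*Protocol article*

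**What the plan says.** Three places in the protocol article describe a wide scope.

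- Discussion: "the study will provide a comprehensive picture of transition needs across all public child psychiatry services in a large French city". The same section calls the prevalence figure a first city-level estimate of access to CAMHS and presents it as essential for quantifying service needs at the transition boundary.
- Abstract, Methods and analysis: the study is "expected to provide one of the first city-level estimates of psychiatric transition needs in France".
- Objectives: the primary objective concerns 17-year-olds living in Nice "who consult specialised CAMHS child and adolescent psychiatry services, relative to the total population of 17-year-olds residing in Nice". No hospital is named here, although the first two secondary objectives do name Lenval.

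The operational definitions are narrower.

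- Primary outcome: patients "who attend the child and adolescent psychiatry services at Lenval University Children’s Hospital, defined as the number of 17-year-olds consulting in 1 year", over all 17-year-olds in the city. The primary-outcome paragraph of the Statistical analysis section repeats the restriction to Lenval.
- Study procedures: the numerator comes from Lenval's own PMSI for 2024. It covers every care setting, emergency assessments included, and has no condition about transition. The denominator is the 2022 census count.
- Inclusion criteria (cohort only): "Considered to be in a potential transition situation to adult mental health services within the following 12 months".
- Recruitment and informed consent: "Screening logs are maintained to document the number of eligible patients approached, included or refusing participation".

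**The concern.** Two separate steps are taken without support.

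The first is from one hospital to the city. The denominator is every 17-year-old in Nice, while the numerator can contain only those seen at Lenval. The abstract justifies the choice of hospital by saying that it is the department's only children's hospital with its own child psychiatry emergency service. That concerns emergencies. It does not say that Lenval provides all public CAMHS care used by Nice residents, and no other provider's data are used.

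The second is from contact to need. A single emergency assessment counts the same as long-term follow-up that will have to continue in adult services. A count of attenders is therefore not a count of young people needing transition.

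The results are to go to regional health authorities and to inform regional planning. A reader who takes the figure as the city's transition need could size a service on a quantity that the study does not measure.

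**Working it through.** The plan states no expected prevalence, coverage share or need share, so there is no figure to reproduce. The check compares definitions and then uses labelled assumptions to show how far apart the quantities could lie.

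**Step 1: what each element measures**

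| Element | Who is counted | Transition need recorded? |
|---|---|---|
| PMSI numerator | All 17-year-old Nice residents with any contact at Lenval, 2024 | No |
| Screening log, as described | Eligible patients approached, included or refusing | Only through eligibility, which requires the transition criterion |
| TRAM at M0 and M6 | Consenting cohort members | Yes, patient-reported appropriateness and readiness |
| 12-month trajectories | Cohort members | Yes: transfer, continued CAMHS care, agreed end of care and other outcomes |

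The first row covers all attenders without information on need. The other rows carry information on need, but only for people selected on it. A share needing transition requires a denominator that includes attenders *not* in a transition situation, and no row supplies one. Every cohort member already meets the criterion, so no cohort proportion can be multiplied by the PMSI count to give the number of attenders who need transition. The cohort also excludes acute cases and those with insufficient French, among others.

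**Step 2: illustration of size**

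- From Sample size estimation: about 160–200 17-year-olds per year at Lenval (not stated to be Nice residents only).
- Assumption: c = Lenval's share of the city's public child psychiatry users aged 17, from 0.5 to 1.0.
- Assumption: q = share of attenders who need transition, from 0.3 to 0.9, the same at Lenval and elsewhere.

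City total = Lenval count / c:
- c = 1.0: 160–200
- c = 0.5: 160/0.5 = 320 to 200/0.5 = 400

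Lenval attenders needing transition = Lenval count × q:
- q = 0.3: 48–60
- q = 0.9: 144–180

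If A is the Lenval count, the city's transition need is (A/c) × q, so contact count / city transition need = c/q:

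| | q = 0.3 | q = 0.6 | q = 0.9 |
|---|---|---|---|
| c = 0.5 | 1.67 | 0.83 | 0.56 |
| c = 0.7 | 2.33 | 1.17 | 0.78 |
| c = 1.0 | 3.33 | 1.67 | 1.11 |

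Incomplete coverage lowers the ratio and counting contact instead of need raises it. Without c and q, even the net direction is unknown. With full coverage (c = 1.0), the contact count still exceeds need by 1.11 to 3.33 times in this range, so the second problem does not depend on the first.

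**Step 3: what an extended log could deliver**

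Over 18 months, 160–200 per year gives at most about 240–300 attenders (160 × 1.5; 200 × 1.5), fewer once restricted to Nice residents. At a share of 50%, the 95% half-width is 1.96 × √(0.25/240) = 6.3 points or 1.96 × √(0.25/300) = 5.7 points. That is usable, and somewhat wider with fewer residents.

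**The case against.** The operational text is clear. Study design, Study procedures, Primary outcome and Statistical analysis all name Lenval, and the Discussion describes the prevalence as access to CAMHS. The Discussion's broad sentence also rests on combining administrative data with clinical follow-up, and the follow-up does address transition. Lenval may in fact be the only public provider for Nice. The single-centre design is listed as a limitation.

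Much of this stands. Two stronger readings that a reader might infer are not supported:

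- *That the study records nothing about transition need.* It does. Eligibility with the log, TRAM and the 12-month trajectories all record it among eligible or enrolled patients. What is missing is the share among all 17-year-old attenders.
- *That the primary figure is a lower bound for CAMHS use in Nice.* The article is silent on Lenval's coverage, and silence does not show that coverage is incomplete. The ratio can also move upward. It puts a 2024 numerator over a 2022 denominator, and a calendar-year count of patients seen at age 17 draws on two birth years, whereas a census counts one year of age.

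The rest of the objection does not remove the point. The limitation is worded as one of generalisability. Residents missed by the numerator, and contact standing in for need, are matters of what the primary figure measures, and neither is disclosed. If Lenval does cover all public services, the article should say so, and the gap between contact and need would remain. The article may condense a fuller description of the log, but a fuller log would not change the wording of the claims.

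**Conclusion.** The point holds as a mismatch between what is claimed and what is measured. The primary estimand is the annual prevalence of any psychiatric service contact at Lenval among 17-year-old Nice residents. The primary objective words it as CAMHS use in general. The abstract and Discussion go further and claim city-level transition need, in the Discussion across all public services. Neither coverage nor need is established by anything described.

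No numerical bias can be stated. The range of 0.56 to 3.33 rests wholly on the assumed ranges for c and q and on q being equal across services. It shows only that the contact count is not a usable stand-in for transition need. Lenval's PMSI remains a sound source for service contact at that hospital, and the cohort's own descriptive aims are unaffected.

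**What to change.** 1. **Wording.** In the primary objective, abstract and conclusions, name the estimand as Lenval-treated (service-contact) prevalence among 17-year-old Nice residents. Either document Lenval's share of public child psychiatry for these residents or delete the claim to cover all public services. State that contact is not transition need. Do not call the figure a lower bound unless coverage is shown to be incomplete.

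2. **Log.** Have the existing screening log record every 17-year-old Nice resident screened, with transition-situation status and the criterion failed. Report the share meeting the transition criterion, with a 95% CI, for the recruitment period. The article gives no working definition of that criterion, so one is needed for the log to be read consistently. Recruitment began in April 2026, so the share should be labelled as starting from the date of the change. Any combination with the 2024 PMSI count should be labelled approximate because the periods differ.

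The cost is a narrower headline claim, one more log line per resident screened, and a brief judgement of transition status for patients who would otherwise not be logged, including those seen only as emergencies. The wording change needs no new data unless the sponsor chooses to document coverage.
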